# Overview

- 1. **Schema**

|  | Patients with chronic respiratory failure receiving NPPV during outpatient visits | | | | | | | |  |
| --- | --- | --- | --- | --- | --- | --- | --- | --- | --- |
|  |  |  |  |  |  |  |  |  |  |
|  | During a routine outpatient visit, the attending physician or physician in charge will provide an overview of the study, to seek for patients who are willing to participate in the research | | | | | | | |  |
|  |  |  |  |  |  |  |  |  |  |
|  |  | Researcher explains the research overview, consenting participants fills out the consent form and are registered | | | | | |  |  |
|  |  |  |  |  |  |  |  |  |  |
|  | At enrollment (baseline)  Primary endpoint: Number of hospitalizations, number of hospital days, and number of unscheduled outpatient visits in the past 3 months  Secondary endpoints: SGRQ score, EQ-5D index, SCAQ responses, respiratory function test, and 6-min walk test | | | | | | | |  |
|  |  |  |  |  |  |  |  |  |  |
|  |  |  |  |  |  |  |  |  |  |
|  |  |  |  |  |  |  |  |  |  |
|  |  | Allocation (allocation adjustment factor: facility) | | | | | |  |  |
|  |  |  |  |  |  |  |  |  |  |
|  |  |  |  |  |  |  |  |  |  |
| Intervention group:  Usual outpatient care + tele-nursing intervention program | | | | |  | Control group:  Usual outpatient care | | | |
|  |  |  |  |  |  |  |  |  |  |
|  |  |  |  |  |  |  |  |  |  |
| Regular outpatient care (once/month)   1. Medical treatment by a physician 2. Health consultation and information by nurses   Remote nursing intervention program (1 time/day, 3 months)  Remote monitoring  Once a day  Observation of information input to the tablet  Input items: Vital signs, respiratory symptoms, food intake, excretion, medication, and physical symptoms other than respiratory symptoms  2. Health counseling and information provision  Health consultation and information provision via videophone once a day for approximately 30 min when triggers are applicable or when the participant wishes | | | | |  | Regular outpatient care (once/month)   1. Medical treatment by a physician 2. Health consultation and information by nurses | | | |
|  |  |  |  |  |  |  |  |  |  |
|  |  |  |  |  |  |  |  |  |  |
|  |  |  |  |  |  |  |  |  |  |
|  |  |  |  |  |  |  |  |  |  |
|  |  |  |  |  |  |  |  |  |  |
|  |  |  |  |  |  |  |  |  |  |
|  |  |  |  |  |  |  |  |  |  |
|  |  |  |  |  |  |  |  |  |  |
|  |  |  |  |  |  |  |  |  |  |
|  |  |  |  |  |  |  |  |  |  |
|  |  |  |  |  |  |  |  |  |  |

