# Methods and duration of the study

# Research design

1. Research design

This is a randomized, controlled trial conducted on two groups of patients: an intervention group using an ICT-based tele-nursing intervention program for patients with chronic respiratory failure receiving NPPV at home (in addition to usual care) and a control group receiving usual care.

1. Rationale for setting up the study design

The purpose of this study is to evaluate the effectiveness of a tele-nursing intervention program for patients with chronic respiratory failure receiving NPPV. To this end, the study design was set up as a randomized, controlled trial based on the hypothesis that the group of patients who undergo the tele-nursing intervention program (intervention group) will have fewer temporary outpatient visits (percentage and number of visits) due to acute exacerbations during the intervention period than the group of patients who receive only usual care (control group).

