
The web-based program in the tele-nursing system consists of a patient site and a researcher site. The tablet terminal at the patient site has (1) a screen for recording daily physical condition, (2) a screen for video calls, (3) a screen for SNS input, and (4) a screen for respiratory rehabilitation information. The researcher's site will have (1) a list of the participant's telemonitoring data and (2) a screen for inputting comments. The researcher can check the participant's daily records and output the changes over time on a summary sheet.

The intervention period will be 24 weeks, and the number of ad hoc visits and readmissions during the past 12 and 24 weeks (primary endpoints) will be examined by the researcher at enrollment, 12 weeks after enrollment, and 24 weeks after enrollment, using the electronic medical record. At enrollment and at regular outpatient visits 12 and 24 weeks after enrollment, researchers will conduct a questionnaire survey about daily life, and perform respiratory function and 6-minute walk tests. In addition, activity meters will be checked 12 and 24 weeks after enrollment to collect data on the average number of steps and patient activity. Respiratory function and 6-min walk tests at enrollment as well as 12 and 24 weeks after enrollment will be performed by the researcher using equipment purchased using the research fund, since these tests are not covered by insurance and are outside the scope of usual medical care. Since the primary endpoints of this study are the number of emergency visits and rehospitalizations due to acute exacerbations of chronic respiratory diseases, the intervention will not be stopped in the event of worsening symptoms due to acute exacerbations. If the participant dies, the intervention is terminated because the study cannot continue. If a participant requests that the intervention be continued after their participation in the program, the intervention may be offered for an extended period of time, regardless of whether the participant is in the intervention or control group.

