# Description of adverse events

Since this study will be an informational and health counseling activity for patients, adverse events from the intervention are likely to be very minimal. However, since respiratory function and 6-min walk tests will be performed during the measurement of secondary endpoints, it is possible that minor adverse events such as temporary worsening of symptoms may occur during these tests. In the event of an adverse event, the attending physician should be notified immediately for necessary action. For all adverse events, the progress during the intervention should be described in a case report, including the name of the adverse event, its severity, the reason it was deemed serious, the date of onset, the date of outcome, the treatment, the outcome, and the causal relationship with the intervention.

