**Criteria and Deadlines for Reporting to the Head of the Research Institution and Principal Investigator**

|  | **Mild/Moderate/Severe (Grade 1/2/3)** | | | **Most severe (Grade 4)** | | **Death** | | **Other medically important conditions** |
| --- | --- | --- | --- | --- | --- | --- | --- | --- |
|  | **Predictable (known)** | **Unpredictable (unknown)** | | **Predictable (known)** | **Unpredictable (unknown)** | **Predictable (known)** | **Unpredictable (unknown)** |  |
|  | **Hospitalization (No / Yes)** | **Hospitalization (No)** | **Hospitalization (Yes)** |  |  |  |  |  |
| **Causal relationship exists** | Report not required | Report not required | First report: Within 10 days  Additional report: As and when necessary | Primary report: Within 72 days  Second report: within 7 days  Additional reports: As and when necessary | | | |  |
| **No causal relationship** | Report not required | Report not required | First report: Within 10 days*  Additional reports: As and when necessary* | Primary report: Within 72 days*  Second report: within 7 days*  Additional reports: As and when necessary* | | | |  |

*On treatment or within 30 days of last protocol treatment date only

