# Methods of data management and self-inspection

# CRF preparation

The researcher will complete and correct the entries on the CRF. The investigator will complete the CRF promptly after the completion of the intervention for each participant. Since the program lasts for 24 weeks, the CRF will be prepared after 24 weeks of intervention. Care should be taken to ensure that the primary and secondary endpoints are covered and that vital signs and information on how the daily evolution of the participant's condition can be clearly and concisely ascertained. In addition, as with the nursing record, videophone information should be recorded such that it can be understood.

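### The reporting window for serious events judged unrelated depends on an undefined last treatment date, so it is unclear for usual-care controls and could differ between the arms

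*Protocol*

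**What the plan says.** The table headed Criteria and Deadlines for Reporting to the Head of the Research Institution and Principal Investigator has one row for causally related events and one for unrelated events. Every reportable cell of the unrelated row carries an asterisk: unpredictable Grade 1 to 3 events with hospitalization, Grade 4 events, and deaths. An entry such as "First report: Within 10 days" stands in both rows, but only the unrelated row adds the asterisk, which reads "On treatment or within 30 days of last protocol treatment date only".

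The protocol defines neither protocol treatment nor its last date. Other sections bear on what that date could be:

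- Research design: the comparator is "a control group receiving usual care".
- Overview, schema: "Remote nursing intervention program (1 time/day, 3 months".
- Overview of the distance nursing intervention program and observations: "The intervention period will be 24 weeks". The same section says that on request "the intervention may be offered for an extended period of time, regardless of whether the participant is in the intervention or control group", with no stated end.
- CRF preparation: "Since the program lasts for 24 weeks, the CRF will be prepared after 24 weeks of intervention".

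On recording, as distinct from reporting upward, Description of adverse events says: "For all adverse events, the progress during the intervention should be described in a case report".

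**The concern.** A window that closes a fixed time after the last treatment works only if every participant has such a date. Half of the planned participants, 17 of 34, are allocated to usual care and have none that the protocol identifies. Causality is judged against the intervention, which controls do not receive. A serious event in a control will therefore nearly always fall in the unrelated row, where the asterisk applies. The likely exception is an event during a study breathing or walking test that a site calls related.

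In the intervention group the date exists, but the protocol gives two programme lengths and allows an open-ended extension.

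What is at stake is even safety oversight. The section on anticipated risks names delayed medical attention as the foreseeable disadvantage of the programme. Harm of that kind could appear as a severe exacerbation or a death that a site puts down to the underlying disease. Those overseeing the trial should receive such reports over the same period in both arms.

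**Working it through.** The protocol states no figure to reproduce, so the check is calendar arithmetic followed by a comparison of sections.

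**Inputs**

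- Footnote allowance: 30 days after the last treatment date.
- Programme length: 3 months in the schema, 24 weeks in the programme overview and in CRF preparation.
- Final scheduled assessment: 24 weeks after enrolment in Survey Schedule, so 24 × 7 = day 168.
- Assumptions: the programme starts at enrolment (day 0); 3 months is about 91 days, or 84 days if taken as 12 weeks; no extension.

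**Intervention group**

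Window end = programme length + 30. Uncovered follow-up = 168 − window end, or 0 if negative.

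- 3 months as 91 days: 91 + 30 = day 121; 168 − 121 = 47 days uncovered.
- 3 months as 84 days: 84 + 30 = day 114; 168 − 114 = 54 days uncovered.
- 24 weeks: 168 + 30 = day 198; none uncovered.

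The two lengths move the closing date by 198 − 121 = 77 days, or 198 − 114 = 84 days.

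**Control group**

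- Strict reading (usual care is not protocol treatment): no window, 0 of 168 days covered.
- Broad reading (usual care is the allocated treatment): covered for all 168 days. Usual care has no end, so the window then has no closing date.

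**Days of the 168-day follow-up covered, with 3 months as 91 days**

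| Programme length | Reading for controls | Intervention | Control | Difference |
| --- | --- | --- | --- | --- |
| 24 weeks | Broad | 168 | 168 | 0 |
| 24 weeks | Strict | 168 | 0 | 168, intervention longer |
| 3 months | Strict | 121 | 0 | 121, intervention longer |
| 3 months | Broad | 121 | 168 | 47, control longer |

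The gap within follow-up thus runs from 0 to 168 days, and its direction depends on the reading. An extension shifts the dates again. It moves the last treatment date later in the intervention group. On the strict reading, a control offered the programme after follow-up would first come on treatment at that point.

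**Do other sections close the gap?**

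- Report to the head of the research institution and the principal investigator sets a general duty for serious events and names no arm. It takes its time limits from the table, which brings the footnote back in.
- Obtaining information has the investigator report serious events to the institution's principal investigator, with no arm or window stated.
- Description of adverse events covers all adverse events. The CRF, however, is prepared after 24 weeks, so it is not a timely substitute for a report.

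**The case against.** The strongest reply is that the table governs reports to the head of the institution and the principal investigator. It does not decide what enters the trial record. Serious events must still be reported under Obtaining information, and all adverse events must be described in the case report, with no arm named. Rows for related events carry no window, and the safety stopping rule counts only related events. Readmissions and unscheduled visits for exacerbation are primary endpoints collected in both arms. All of this stands.

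It is also fair that the phrase about progress during the intervention need not exclude controls. Research design and the sample size section use the intervention period as a calendar period common to both groups. A clarifying sentence is enough there.

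The 3-month figure appears in the schema, whereas several sections use 24 weeks, and the tablet charging cost assumes 180 days. The 47-day shortfall therefore depends wholly on the schema figure. The control-arm question remains under either length.

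A reader might infer that deaths will be reported unequally by arm, that control deaths are lost, or that the programme could be made to look harmful. The documents do not support these readings. Unequal reporting follows only if usual care is not protocol treatment or if the schema's length governs. The separate recording duties keep deaths within reach of the trial data. No section plans to compare the arms on these reports.

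**Conclusion.** The point holds as a defect in a stated rule. The window for unrelated serious events is undefined for 17 of 34 planned participants and ambiguous for the other 17. Depending on the reading, controls have anything from no window to all 168 days of follow-up. The intervention window closes at about day 121 or at day 198.

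This rests on the protocol giving no definition of protocol treatment, on the programme starting at enrolment, and on no extension being taken. With 24 weeks and usual care counted as treatment, coverage within follow-up is equal, so a difference between arms is possible but not certain. The effect is confined to reports of events judged unrelated. Sample size, endpoints and planned analyses are untouched.

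**What to change.** - Replace the footnote with one window anchored to enrolment and identical in both arms: from enrolment to the final scheduled assessment plus 30 days. With the 24-week assessment this is day 168 + 30 = day 198 for everyone. List events during any extended programme separately, whichever group the participant was allocated to.
- In Description of adverse events, state that adverse events are described for both groups over the study period.
- Reconcile the programme length across the schema, the programme overview and CRF preparation so that a single length is stated.

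The cost is a footnote, a sentence, and a reconciliation that the protocol needs in any case. The downside is a few more reports from control participants, who are already assessed at 12 and 24 weeks.

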# Reporting to collaborating institutions

1. In the case of multicenter collaborative research, the principal investigator shall report the adverse event/failure to the principal investigators of the research institution where the adverse event/failure occurred and collaborating research institutions, using the Serious Adverse Event Report Form; in addition, a report shall be sent to the head of the research institution and Ethics Committee.
2. The principal investigator of the research institution will take necessary measures in response to instructions from the head of the research institution.

# Evaluation items and methods

# Primary endpoints

Since the purpose of this study is to verify the effectiveness of a tele-nursing intervention program for the prevention of acute exacerbations of chronic respiratory diseases, it is necessary to set the status of acute exacerbations as an evaluation item. Acute exacerbations cannot be determined simply by considering the number of temporary visits and rehospitalizations separately, and thus, the primary endpoints of this study are the statuses of temporary outpatient visits (rate and number of visits) and rehospitalizations (rate and number of hospitalizations) due to acute exacerbations in the past 12 and 24 weeks, as well as the reasons for the outpatient visits or hospitalizations at enrollment (baseline) and 12 weeks after enrollment. The data will be collected from the patients themselves at baseline, 12 weeks after enrollment, and 24 weeks after enrollment. However, if the patient's complaint is unclear, it will be collected from the patient's medical record.

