# Objective

The effectiveness of an ICT-based tele-nursing intervention program for patients with chronic respiratory failure undergoing NPPV in home care will be examined in terms of the number of readmissions and occasional visits due to acute exacerbations or chronic respiratory diseases, with readmission and occasional visit rates as primary endpoints.

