# Basis for setting

The primary hypothesis of this study is: A group of patients with chronic respiratory failure receiving NPPV with a tele-nursing intervention program (intervention group) will have fewer temporary outpatient visits (percentage and number of visits) due to acute exacerbations during the intervention period than a control group receiving only usual care (Figure 1). Based on the literature [24], we assumed that the average number of visits to the emergency department due to acute exacerbations of chronic respiratory diseases would be 2.4 visits/year for NPPV users and 1.6 visits/year for NPPV non-users to reduce the number of outpatient visits by 1.0 visit/year. The significance level, power of the study, and standard deviation of the number of improvement of visits are 5%, 80%, and 1.0 visit/year, respectively. In addition, assuming a dropout rate of 10% of the total number of patients, the intervention and control groups were calculated to require 17 patients each, for a total of 34 expected enrollees in both groups.

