# Statistical analyses

# Statistical analysis methods

Data on basic participant characteristics will be examined for normality using the Kolmogorov-Smirnov test, and the differences between the means or medians for the data in the intervention and control groups will be compared using the *t*-test, based on the normality of the data. Fisher's exact test will be used to compare the primary endpoints of temporary outpatient visit and readmission rates between groups, and student *t*-test will be used to compare the number of temporary visits and readmissions between groups. Paired *t*-tests will be used to compare changes in secondary endpoints at baseline, 12 weeks after enrollment and intervention initiation, and 24 weeks after enrollment and intervention initiation (at the end of the intervention period). The analysis will be conducted using a personal computer with Microsoft Windows 8.1 OS installed and IBM SPSS version 21.0 statistical software, with a two-tailed significance level of 5%.

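### The primary endpoint is defined in five conflicting ways and can be tested up to eight times at an undivided 5%, with no rule for which result decides the trial

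*Protocol*

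**What the plan says.** Five places in the protocol define what is primary:

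- **Overview, schema:** "Primary endpoint: Number of hospitalizations, number of hospital days, and number of unscheduled outpatient visits in the past 3 months". These are three counts, one of them found nowhere else as primary (days in hospital).
- **Objective:** effectiveness is to be examined through numbers of readmissions and visits, but the label is attached to rates: "with readmission and occasional visit rates as primary endpoints".
- **Overview of the distance nursing intervention program and observations:** numbers of visits and of readmissions, at 12 and 24 weeks, are marked as primary; rates are not mentioned.
- **Primary endpoints:** "the statuses of temporary outpatient visits (rate and number of visits) and rehospitalizations (rate and number of hospitalizations) due to acute exacerbations", at 12 and 24 weeks. The section adds that exacerbations cannot be judged from visits and readmissions taken separately.
- **Basis for setting (9.2):** the primary hypothesis is that the intervention group "will have fewer temporary outpatient visits (percentage and number of visits) due to acute exacerbations during the intervention period". This covers visits only, but in two forms. The calculation uses one form, the number: the aim is "to reduce the number of outpatient visits by 1.0 visit/year", and "The significance level, power of the study, and standard deviation of the number of improvement of visits are 5%, 80%, and 1.0 visit/year, respectively".

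Section 10.1 compares the visit and readmission rates by Fisher's exact test and the two numbers by t-test, "with a two-tailed significance level of 5"%, and gives no time point for these four comparisons. Section 10.2 plans an analysis at 12 weeks, by the same methods, to see whether the main objective is met. It allows early termination if superiority is judged sufficient.

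The schema also describes a "Remote nursing intervention program (1 time/day, 3 months"), while the intervention overview and section 11.1 give 24 weeks.

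**The concern.** No section says which of these results decides the trial. There is no ordering, no division of the 5%, no requirement that all succeed, and no defined composite. Any one significant comparison among up to eight (more if days in hospital are counted) could be reported as the primary result, with some section of the protocol to support it. A mixed outcome, such as fewer visits but more admissions, would have no agreed reading. Because section 10.2 ties the 12-week analysis to the main objective and to early termination, the 12-week tests are a real route to declaring success.

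**Working it through.** **1. What the sample size assumes.** Inputs from section 9.2: difference 1.0 visit/year, SD 1.0, 5%, power 80%, dropout 10%, taken as given here.

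n per arm = 2(z₀.₉₇₅ + z₀.₈₀)² × SD²/difference² = 2(1.960 + 0.842)² × 1.0²/1.0² = 15.70, so 16.

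With dropout: 15.70/0.90 = 17.4. Rounding up gives 18 per arm (36 in total), against the stated 17 (34). An exact t-test calculation needs 17 per arm before dropout and 19 after; a one-sided test needs 13 and 15. The stated figure is therefore within one per arm of a single two-sided test of the number of visits at an undivided 5%. Nothing was set aside for further primary tests.

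**2. Number of tests.** 2 outcomes × 2 forms × 2 windows = 8. Section 10.1 supplies four; the 12-week set comes from section 10.2.

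**3. Independence figure.** 1 − 0.95⁸ = 33.7%; for four tests, 1 − 0.95⁴ = 18.5%. Neither describes this trial. The 12-week window lies inside the 24-week window, the rate and the number come from the same events, and Fisher's test at this sample size rejects only about 2% of the time under no effect.

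**4. Simulation under no effect.** From the protocol: 17 per arm, 2.4 visits/year in both arms (2.4 × 24/52 = 1.11 expected visits in 24 weeks), t-test for numbers, Fisher's test for percentages. Assumed: the readmission rate, the between-patient dispersion (gamma frailty with variance 0, 0.5 or 1.0), and both windows complete for everyone. The table gives the chance of at least one p<0.05.

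| Assumed readmissions | Eight tests, dispersion 0 / 0.5 / 1.0 | Four 24-week tests, same order |
|---|---|---|
| 30% of visits | 15.7 / 14.8 / 13.5% | 9.8 / 9.7 / 9.0% |
| 50% of visits | 14.9 / 13.9 / 13.2% | 9.4 / 8.9 / 8.8% |
| Separate events at half the visit rate, shared frailty | 17.3 / 15.7 / 15.2% | 11.0 / 10.0 / 10.3% |
| 10-80% of visits, 15 or 17 per arm | about 10-18% | about 7-11% |

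(15 per arm reflects the planned dropout: 17 × 0.9 = 15.3.) The t-test on the 24-week number of visits alone rejects in 4.3-5.1%. All figures count significance in either direction; about half would favour the intervention.

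**5. The 12-week look on its own.** With a single endpoint tested at 5% at both 12 and 24 weeks (information 12/24 = 0.5, normal approximation), the false-positive rate is 8.3%. Naming one endpoint is therefore not enough if section 10.2 stays as it is.

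**The case against.** **The primary hypothesis already singles out outpatient visits.** It does, and the calculation narrows this to their number. But the hypothesis itself carries a percentage as well, so a reader who infers that it names the number alone goes too far. It also conflicts with four other sections and is tied to no decision rule.

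**Section 10.1 plans four tests, not eight.** This stands. A reader might infer that section 10.1 fixes eight primary tests; it gives four, with no time point. Eight is a maximum that needs section 10.2. The four 24-week tests alone still give 7-11%.

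**The Objective is closer to the other sections than its last clause suggests.** A reader might infer that it names rates only. The same sentence says that numbers will be examined; the conflict lies in which of the two carries the primary label.

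**There is a reason to keep both outcomes.** The Primary endpoints section argues against viewing visits and readmissions separately. That would justify a combined count, or a rule that both must succeed, under which there would be no inflation. The protocol defines neither, and section 10.1 tests the outcomes separately.

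**An adjustment could sit in a statistical analysis plan.** It could, so the absence of an adjustment is not by itself the finding. The finding is that the protocol fixes conflicting primary endpoints, the tests, the level and the 12-week repetition.

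**Conclusion.** The point holds. The primary endpoint is defined inconsistently, and the tests that the protocol fixes allow up to eight unadjusted routes to success. The false-positive rate exceeds 5% in every setting examined: roughly 10-18% for eight tests and 7-11% for the four 24-week tests, against about 5% for one visit count at 24 weeks. The ranges rest on an assumed readmission rate and dispersion, neither of which is in the protocol, and on a 12-week analysis that includes everyone. A reader might take 34% as the size of the problem. That figure requires independent tests, which nested windows and shared events rule out; it serves only as an upper figure.

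**What to change.** - Name one primary endpoint, one form and one time point. The choice that matches the sample-size basis is the number of temporary outpatient visits due to acute exacerbation, per participant, over 24 weeks. A single prespecified count combining visits and readmissions would also answer the rationale in the Primary endpoints section, but the basis in section 9.2 would then have to be restated.
- Make the visit percentage, the readmission rate and number, days in hospital and all 12-week results secondary, with no confirmatory claim.
- Amend section 10.2 so that the 12-week analysis makes no unadjusted superiority claim and cannot stop the trial for superiority at an unadjusted 5%.
- Align the schema, Objective, intervention overview, Primary endpoints section, 9.2 and 10.1. Reconcile the 3-month programme in the schema with the 24 weeks elsewhere; the primary time point should follow from that reconciliation.

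**Cost.** Section 27 treats changes that affect the primary endpoints or the evaluation of efficacy as amendments, so ethics review and institutional approval are needed. A significant readmission or 12-week result could no longer be called primary. The sample-size basis does not change with the visit count.

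Keeping all eight tests would cost far more. Under Bonferroni, each is tested at 0.05/8 = 0.00625, which needs 26 per arm, or 29 with dropout (58 in total against 34). With 17 completers per arm, power for the planned effect would fall from about 81% to about 50% (t-test).

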# Survey Schedule

|  | **Evaluation item** | **Survey schedule** | | |
| --- | --- | --- | --- | --- |
|  |  | **At enrollment**  **(Baseline)** | **12 weeks after enrollment** | **24 weeks after enrollment** |
| **Interview or medical record** | Basic patient information | ◯ |  |  |
|  | Occasional visits and readmissions in the past 12 weeks | ◯ | ◯ |  |
|  | Occasional doctor visits and readmissions in the past 24 weeks | ◯ |  | ○ |
| **Questionnaire** | SGRQ | ◯ | ◯ | ◯ |
|  | EQ-5D | ◯ | ◯ | ◯ |
|  | SCAQ | ◯ | ◯ | ◯ |
| **Objective assessment items** | Respiratory function test | ◯ | ◯ | ◯ |
|  | 6-min walk test | ◯ | ◯ | ◯ |
|  | Average number of steps, activity level |  | ◯ | ◯ |

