# Centralized evaluation system

This study does not use a centralized evaluation system.

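### The protocol gives two incompatible sources for the primary visit and readmission counts, and does not specify that reasons for events are recorded at 24 weeks

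*Protocol*

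**What the plan says.** Three places in the protocol deal with where the primary counts come from.

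- The Overview of the distance nursing intervention program and observations says that ad hoc visits and readmissions, named there as the primary endpoints, "will be examined by the researcher at enrollment, 12 weeks after enrollment, and 24 weeks after enrollment, using the electronic medical record".
- The Primary endpoints section says of the same endpoint: "The data will be collected from the patients themselves at baseline, 12 weeks after enrollment, and 24 weeks after enrollment". It adds a fallback: "However, if the patient's complaint is unclear, it will be collected from the patient's medical record".
- The Survey Schedule puts both look-back periods under the row label "Interview or medical record", with no order of priority.

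The endpoint is cause-specific: the Primary endpoints section limits it to visits and rehospitalizations "due to acute exacerbations in the past 12 and 24 weeks". The same sentence adds the "reasons for the outpatient visits or hospitalizations at enrollment (baseline) and 12 weeks after enrollment". It does not name 24 weeks there.

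On independent assessment, the protocol says: "This study does not use a centralized evaluation system".

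**The concern.** The count of events is the primary outcome, so the rule for finding events has to be the same for every participant. Here two sites could each follow the protocol and count different events for the same patient.

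The choice also matters for bias. The comparator is usual care with no sham, so patients know their arm. Intervention patients enter their condition on a tablet every day and are telephoned if entries stop; controls keep no such log. The researchers who run the monitoring and counselling also collect the endpoint, and no blinding of the assessor is described. If counts rest on what patients report, and on a researcher's judgement of when the report is unclear enough to open the record, completeness can differ by arm. Such a difference would enter the primary comparison directly.

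The missing 24-week entry for reasons matters because an event can be assigned to the endpoint only if its cause is known.

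**Working it through.** **1. Can the source statements be read together?**

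| Place | Source of counts | Time points |
|---|---|---|
| Overview of the program | Electronic medical record | Enrollment, 12 and 24 weeks |
| Primary endpoints | Patient; record only if unclear | Baseline, 12 and 24 weeks |
| Survey Schedule | Interview or record | Baseline, 12 and 24 weeks |

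The events, look-back windows and time points are the same, so the rows do not describe different data. They do not describe one sequence either: the Overview has the researcher use the record each time, while the Primary endpoints section does so only on a condition. That condition has no criterion. The rules diverge in practice. A visit that is in the record but that a patient clearly, though wrongly, omits is counted under the Overview and not under Primary endpoints, because a clear account triggers no look-up. A visit to another hospital that the patient reports is counted under Primary endpoints and may be missed under the Overview.

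**2. Does another section settle it?** CRF self-inspection requires the CRF to be checked against source documents, including medical records, and any discrepancy to be explained in a report. It does not say which value stands.

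**3. What could a reporting gap amount to?** The inputs, all from Basis for setting, are 2.4 visits/year in NPPV users, a planned reduction of 1.0 visit/year and 17 patients per arm. The planned size is reproduced to rounding: 2 × (1.96 + 0.84)² × 1.0² / 1.0² = 15.7 per arm; 15.7 / 0.9 = 17.4. The point here does not depend on that figure.

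- Expected visits over 24 weeks: 2.4 × 24/52 = 1.108.
- Planned effect over 24 weeks: 1.0 × 24/52 = 0.4615.
- Assumed extra under-reporting in one arm, not from the protocol: 10-20%.
- Shift in the difference: 0.10 × 1.108 = 0.11 to 0.20 × 1.108 = 0.22 visits.
- Share of the planned effect: 0.1108 / 0.4615 = 24% to 0.2215 / 0.4615 = 48%.

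**4. What would that do to the t-test?** A simulation assumed Poisson counts with mean 1.108, no true effect, 17 per arm, a two-sided 5% Student t-test and 40,000 replicates.

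| Share of events reported in one arm (other arm 100%) | Spurious difference | Rejection rate |
|---|---|---|
| 100% | 0 | 5.1% |
| 90% | 0.11 | 5.8% |
| 80% | 0.22 | 9.5% |
| 70% | 0.33 | 16% |

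The false difference favours the intervention if that arm under-reports, and works against it if the control arm does. At 80% reporting, significant results in favour of the intervention move from 2.5% to 9.0% in the first case and to 0.5% in the second.

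**5. Reasons at 24 weeks.** Reasons taken at 12 weeks can cover events up to week 12. For events in weeks 13 to 24 the Primary endpoints section names no time at which the reason is taken, yet the 24-week endpoint includes only events caused by acute exacerbation.

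**The case against.** The strongest reply is that this is loose wording around an adequate process. The record is already to be reviewed, the CRF is checked against source documents in both arms, and a disagreement between patient and record should surface. That is fair as far as it goes, and it makes the picture of wholly unchecked recall too strong. But surfacing a disagreement is not resolving it, and no rule says which count enters the analysis.

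Some stronger readings are tempting and do not hold.

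- A reader might infer that cause is not recorded at 24 weeks, so that later events cannot be classified. The protocol does not say that. Its general sentence on data collection includes 24 weeks, and CRF preparation requires the primary endpoints to be covered. What is supported is that reasons at 24 weeks are not specified.
- A reader might infer that controls must recall 24 weeks unaided. The Schema gives both arms monthly outpatient care with physician and nurse contact, the Survey Schedule also asks both arms at 12 weeks, and the record is available as a fallback.
- A reader might infer that any miscount would be beyond repair. The records exist for both arms and could be re-abstracted or used in a sensitivity analysis.
- A reader might take the 10-20% gap as an estimate. Nothing in the protocol supports it, and if controls are the ones who forget more, the bias runs against the intervention. At a 10% gap the false-positive rate barely moves.

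**Conclusion.** The contradiction stands. The Overview and the Primary endpoints section set different sources for the same primary counts at the same times, and neither the Survey Schedule nor the CRF check resolves it. Following the Primary endpoints rule leaves room for completeness of counting to differ by arm. That patients know their arm is an inference from the design, not a statement in the protocol, but it is a safe one for a tablet and videophone program against usual care.

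The size and direction of any bias cannot be derived from the protocol. The figures of 0.11-0.22 visits, or 24-48% of the planned effect, show only that a modest gap would be large relative to the effect sought. They rest on an assumed gap and on carrying the 2.4 visits/year over to 24 weeks.

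The time points for reasons are incomplete. This is a gap in the specification, not proof that the data will be absent. Both matters should be corrected.

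**What to change.** In the Primary endpoints section, make the medical record the source of visit and readmission counts for all participants in both arms at baseline, 12 and 24 weeks, as the Overview already plans. Use the patient interview only to identify visits or admissions at other hospitals, and confirm those from records. Change the row label in the Survey Schedule to match. Add 24 weeks to the time points at which reasons for visits and hospitalizations are recorded, and carry this into the CRF.

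The cost is wording in the protocol and CRF, since the record review is already planned, plus a small effort to confirm visits made elsewhere. Treatment, sample size and visit schedule do not change. Naming the record as the source does not blind the person who abstracts it; it removes the dependence on patient recall and on an undefined trigger for looking further.
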